### The secondary outcome measures are:

Gradual onset Continuous Performance Task (target accuracy, raw score)Stop Signal task (time interval for successful stop, raw score)
Flanker task (reaction time in incongruent flanker trials – congruent flanker trials, raw scores)Cross-modal Stroop – Mixed Signals (reaction time in response conflict trials, raw score)WAIS IV Digit Span, forwards and sequencing (raw scores)Spatial Working Memory task (accuracy, raw score)DKEFS Verbal Fluency, phonemic and semantic subtest (raw scores)Reinforcement Learning task (bias index)WMS IV Logical Memory I & II immediate recall (sum of learning trials, raw score)WMS IV Logical Memory I & II delayed recall (sum of recall trials, raw score)Walking Behavior Measure (raw score)Self-efficacy Assessment (two scales, raw scores)Falls Efficacy scale (raw score)Timed Up and Go task –TUG (time to completion, raw score)SF-12 (raw score)Cognitive Failures Questionnaire (raw score)Pittsburg Sleep Quality Index (raw score)Mindful Attention Awareness Scale – MAAS (raw score)Breath Counting task (accuracy, raw score)

The primary analysis time point is V2, the post-training assessment. The secondary analysis time point is V3, the follow-up assessment.

The primary statistical analysis methodology is a linear mixed model approach. We will first compare treatment and active control groups in the ITT population to determine if any differences in baseline demographic, characterization, outcomes variables, or total program use time remain after the randomization process. Any such factors that show trend level significant differences (*p* < 0.1) will be noted and used as covariates in the linear mixed model analysis. We will examine the data from each outcome measure using a linear mixed model with group and time as fixed factors, site as a random factor, and co-variates as necessary from the baseline analysis. Missing data will be handled with an iterative maximum likelihood procedure to optimally estimate model parameters. The key value for significance will be the group by time interaction factor for the model.

The criterion for statistical significance is *p* < 0.05. Results with *p* < 0.1 will be described as trends.

To evaluate the effect of the intervention on executive function we will conduct the analysis based on the pre-training (baseline) and post-training data. Finding a significance level of *p* < 0.05 on the primary executive function outcome measure will support that the intervention improves executive function in the population.

To evaluate the endurance of effects following completion of the intervention we will conduct the analysis based on the pre-assessment (baseline) and follow-up assessment data. We will conduct confirmatory analyses based on the post-assessment (completion) and follow-up assessment data to evaluate the magnitude of change (further increase or decline) over the no-contact follow-up period.

To evaluate and identify specific populations of treatment responders and non-responders we will conduct exploratory data analyses post-hoc to examine predictors of treatment gain and predictors of lack of treatment gain based on baseline participant demographic, cognitive, and functional measures, as well as on learning rate and plateau performance measures derived over the course of the intervention usage. We will initially employ single regression models to identify variables that predict change in cognitive and functional assessments, and then use generalized linear modeling to explore combinations of predictors of treatment gain or lack of gain.

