### Randomization

Participants will be randomized after the baseline visit and before the planned first day of program use. All V0 and V1 data for each participant must be fully monitored, with all queries resolved, before randomization may take place. We will use a randomization server (sealedenvelope.com) that implements the random permuted blocks within strata procedure [49, 50] with strata as age (*Older Adults 65–74* or *Older Adults* ≥ 75 years of age), allocation ratio is 1:1. Participants who are randomized to the experimental treatment group will also be randomized to either receive version 1 (experimental treatment with performance feedback) or version 2 (experimental treatment without performance feedback); at the mid-training assessment, participants will undergo a reversal of the version type such that all participants completing the entirety of the training will have trained on both versions of the experimental training program. The Site Coordinating Center will issue a randomization assignment at the appropriate time. This approach represents a best practice approach to randomization, implementing an automated centralized group assignment procedure with allocation concealment, and effective separation of sequence generation and allocation concealment.

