**Fig. 3 Fig3:**
[figure not shown]
Version A.1 of TAPAT with performance feedback provide every ~ 2 min in the form of an accumulated score (max = 20 per two minutes; total score max = 100)

All training sessions will consist of the three variations of TAPAT to provide variety during each training session. A summary of the training schedule is provided in Table 1.

**Table 1 Tab1:** Training Schedule for a participant randomized to receive TAPAT with feedback in the first half of training

Sessions 1–18	TAPAT with Feedback (v.A.1)	(32 min/session)
	TAPAT (10 min) > 60 s break> TAPAT (10 min) > 60 s break > TAPAT (10 min)	
V1.5	Mid-training assessment (V1.5) Subset of assessments administered in-person.	
Sessions 19–36	TAPAT without Feedback (v.A.2)	(32 min/session)
	TAPAT (10 min) > 60 s break> TAPAT (10 min) > 60 s break > TAPAT (10 min)	

*Active Control Program (commercially-available computer games):* The active control program is composed of 6 commercially available computer games and is designed to: 1) be a face-valid approach to treating cognitive remediation age-related decline (analogous to crossword puzzles for age-related cognitive decline), ensure that participants remain blind to group affiliation, and match the experimental treatment program in halo or expectation-based influence on performance in neuropsychological outcome measures; 2) match the experimental treatment program in overall program use intensity, time-spent attending, delivered rewards, and overall engagement; and 3) provide a comparison group that matches the experimental treatment group on the aforementioned attributes, but without the known therapeutic elements.

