### Data management

We will take all standard and appropriate steps to protect the privacy and confidentiality of participants in this trial. All data collected in this study (with one small exception for electronic usage data captured directly from program use, discussed below) will be from clinician- or psychometrician-administered structured interviews, neuropsychological or functional assessments. Following consent, each participant will be assigned a standardized Participant Identification Number (PIDN). All study-related data will be recorded into a secure, web-based electronic case report form (eCRF) at each site. This system meets all relevant privacy and security standards for electronic clinical trial data entry and storage, as well as the Health Insurance Portability and Accountability Act (HIPAA) standards for confidentiality and privacy. All eCRF data entry will use the only PIDN and not the participant name, Each site will transcribe and upload de-identified data and de-identified source documentation into the study database for the purpose of data monitoring.

To help meet the highest standard of clinical trial management, a Data Safety Monitoring Board (DSMB) independent of the Sponsor and/or study Principal Investigator(s) was established to provide independent overview of safety data, aggregate study data, data management processes, and a priori analyses of primary and secondary endpoints. A DSMB Chairperson shall be appointed in advance to document member attendance and study outcomes (including the statistical methods employed to complete analyses).

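### Total program use time accrues after randomisation, yet it is screened as a baseline factor and can enter the primary ITT model at p<0.1

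*Protocol article*

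**What the plan says.** The Data analysis section, in the paragraph on primary methodology that follows the list of secondary outcomes, first compares the arms in the ITT population to determine "if any differences in baseline demographic, characterization, outcomes variables, or total program use time remain after the randomization process". It continues: "Any such factors that show trend level significant differences (*p* < 0.1) will be noted and used as covariates". The receiving model is a linear mixed model "with group and time as fixed factors, site as a random factor, and co-variates as necessary from the baseline analysis", and "The key value for significance will be the group by time interaction factor for the model". This is the primary method, and nothing in the article confines adjustment for use time to a secondary or sensitivity analysis.

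Two other sections fix when use time arises. Under Randomization: "Participants will be randomized after the baseline visit and before the planned first day of program use". Under Data management, use is recorded as "electronic usage data captured directly from program use". The Description of treatment program adds that the control is meant to "match the experimental treatment program in overall program use intensity, time-spent attending, delivered rewards, and overall engagement".

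**The concern.** A quantity that starts to accrue only once a participant uses the assigned program has no baseline value. It cannot be an imbalance left over from randomisation. If the arms differ in it, the difference arose after assignment and may be an effect of the program. Use may also reflect motivation: the Weaknesses section says that low motivation could hold up completion of the self-initiated training, and motivation could plausibly affect test gains too.

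If the treatment effect is estimated conditional on such a variable, any benefit that works through engagement is removed and a non-causal path through motivation can open. The primary test would then no longer address the ITT comparison that the plan names as primary. The form of the model, and so the quantity estimated, would also depend on a test of post-randomisation data.

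**Working it through.** The documents give no use-time data and no figure on this point to reproduce. From the protocol: 120 participants, 1:1 (60 per arm), planning effect 0.50 SD of change, alpha 0.05 (taken as two-sided), entry threshold p<0.1. Assumed: true use difference d between arms of 0.3 to 0.5 SD, and within-arm correlation r of use with change of 0.2 to 0.4.

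**1. Use time as a main effect only.** Write each score as group, time and group-by-time terms plus γ·U, where U is use time, constant across visits. In the pre-to-post change γ·U cancels, so with complete data the group-by-time estimate cannot move. Simulated mixed models (60 data sets, participant intercept, site omitted, use 0.5 SD higher on TAPAT, slope 0.3) gave these mean group-by-time estimates:

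| Data | No covariate | Main effect | Use × time |
|---|---|---|---|
| Complete | 0.476 | 0.476 | 0.318 |
| Use-related missing V2 | 0.498 | 0.499 | 0.362 |

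With missing data, the main effect moved the estimate by at most 0.0125 in any one data set.

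**2. Chance that use time enters.** From t-test power at alpha 0.10 with 60 per arm: 10% if d = 0, then 29%, 50%, 70% and 86% for d = 0.2, 0.3, 0.4 and 0.5.

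**3. Bias of the whole rule if use time acts on change** (by-time term or change score), total effect zero. The observed use difference D is roughly normal with mean d and SD s = √(2/60) = 0.183. It passes the screen when |D| exceeds c = 1.658 × 0.183 = 0.303. Adjustment subtracts about r·D, and only when D passes, so the size of the bias is r·M. Here M = d·Φ(a) + s·φ(a) with a = (d − c)/s; the opposite tail is negligible.

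- d = 0.3, r = 0.2: M = 0.3 × 0.494 + 0.183 × 0.399 = 0.221; bias 0.044.
- d = 0.4, r = 0.3: M = 0.4 × 0.703 + 0.183 × 0.346 = 0.344; bias 0.103.
- d = 0.5, r = 0.4: M = 0.5 × 0.860 + 0.183 × 0.223 = 0.471; bias 0.188.

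**4. Type I error.** If the covariate always entered, bias would be d·r with SE = √[(4/120)(1 − r²)/(1 − R²)] and R² = (d²/4)/(1 + d²/4). For d = 0.4 and r = 0.3: 0.12/0.178 = 0.68, rejection 10.4%. The rule itself, screen included, was simulated (20,000 runs per row):

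| d | r | Bias, rule | Type I, rule | Type I, always adjusted |
|---|---|---|---|---|
| 0 | 0.2 to 0.4 | 0 | 4 to 5% | 5% |
| 0.3 | 0.2 | 0.044 | 5.4% | 6.3% |
| 0.4 | 0.3 | 0.10 | 8.8% | 10.4% |
| 0.5 | 0.4 | 0.19 | 19.2% | 21.3% |

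A separate run of 10,000 gave 5.6% for the second row, hence about 5.5%.

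**5. Direction.** At d = 0.4 and r = 0.3, false rejections in favour of TAPAT are 0.5% if TAPAT use is higher and 8.0% if it is lower.

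**6. With a true effect of 0.50**, again letting use act on change (4,000 runs per case; use tied to change by a slope of 0.3, by shared motivation, or by both), power without the rule is about 78%:

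| TAPAT use | Mean estimate under the rule | Power |
|---|---|---|
| 0.3 SD higher | 0.40 to 0.46 | 62 to 71% |
| 0.5 SD higher | 0.31 to 0.42 | 41 to 60% |
| 0.3 SD lower | 0.54 to 0.59 | 84 to 91% |
| 0.5 SD lower | 0.59 to 0.70 | 88 to 98% |

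**The case against.** The best defence is that the methodology paragraph names no covariate-by-time term, change score or ANCOVA. Its plainest reading is a covariate main effect, and step 1 shows that this leaves the key estimate where it was. The design also works against a use difference: the control is built to match TAPAT on use, both arms are asked for 36 sessions, and weekly check-ins support adherence. Without a true difference, use time enters about one time in ten and causes no bias.

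All of this stands, and it limits the size of the problem. A reader might infer that the plan as written certainly breaks the randomised comparison; the documents do not support that, because the damaging form of the model is possible but not stated. The defence does not justify keeping use time in the rule. In the harmless form the adjustment does nothing for the key test, and in the form where it does something, it conditions on a possible consequence of treatment.

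**Conclusion.** The sentence is wrong as written: a post-randomisation variable is placed in a baseline screen that feeds the primary ITT model. Whether the primary estimate moves depends on an unstated choice. It does not move with a main effect and complete data. With a by-time or change-score form, bias is about 0.04 to 0.19 SD (9% to 38% of the planning effect: 0.044/0.50 and 0.188/0.50) and type I error about 5.5% to 19%. These ranges rest on assumed use differences of 0.3 to 0.5 SD and correlations of 0.2 to 0.4, neither of which the documents supply. With no use difference there is no bias.

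Two further inferences go too far. Type I errors of 10% at the middle assumptions or 21% at the top would apply only if use time always entered; the screen lowers them to about 9% and 19%. Nor does the rule simply favour a false efficacy claim: it does so only if TAPAT participants train less, and otherwise it works against TAPAT. The p<0.1 screen of variables truly measured at baseline is a separate matter. Those variables precede assignment, and no numerical harm from screening them is shown here.

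**What to change.** Delete total program use time from the factors screened for the primary ITT model. Report use time descriptively by arm, or analyse it in an exposure analysis labelled as secondary. The Fully-Trained population already serves questions about the amount of training received.

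The cost is one sentence in the protocol, and in the analysis plan if it repeats the rule. The sample size of 120 and the rest of the model stay as they are. With use time left out, the simulations gave a mean effect of about 0.50 under the planning assumption, power of about 78% and type I error of about 5%.

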The current study is designed to the highest standard of RCT (e.g., blinded and deals with appropriate allocation concealment). Moreover, this protocol will measure immediate as well as lasting benefits of treatment. Lastly, many previous studies lacked statistical power due to a small sample size. ALERT is appropriately powered to detect improvements in targeted cognitive operations. We have statistically powered the study to detect a between groups Cohen’s d effect size of 0.50 on an outcome measure, calculated as the between group difference in the treatment effect means (post-assessment score minus pre-assessment score) divided by the pooled standard deviation of the observed test-retest reliability. This effect size translates, for example, in an improvement of 5.8 points (on an IQ-like index score) within the treatment group versus an improvement of 1.0 point within the active control group, with both groups showing a variance of 10 points (2/3 of a standard deviation, as observed in other composite cognitive performance data) from pre-assessment to post-assessment. Recently published studies that examined the efficacy of the core exercise (TAPAT) in participants with acquired brain injury (*n* = 40) documented effect sizes of 0.75 [32] and 0.69 [33] on the composite attention measure; we believe this is a reasonable estimate of the plausible effect size in this trial. Also, a recent meta-analysis of the effect size of cognitive rehabilitation documented an average between groups effect size of 0.31 [58] in the population of studies used to support the practice guidelines for cognitive rehabilitation [59, 60]. Based on this analysis, we will enroll 120 participants into the trial. We intend to enroll equally from each site (60 per site).

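### As stated, the primary mixed model names site as its one random factor and has no participant term, so a literal fit overstates the standard error of the decisive group-by-time test

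*Protocol article*

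**What the plan says.** The Data analysis section of the Protocol article lists the terms of the primary model: each outcome is examined "using a linear mixed model with group and time as fixed factors, site as a random factor", with covariates added where the baseline comparison calls for them. The deciding test follows: "The key value for significance will be the group by time interaction factor for the model". For the efficacy claim, "we will conduct the analysis based on the pre-training (baseline) and post-training data", so each participant contributes up to two records. On incomplete data the article says: "Missing data will be handled with an iterative maximum likelihood procedure to optimally estimate model parameters". The threshold is also given: "The criterion for statistical significance is *p* < 0.05". Sidedness is not stated.

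The sample size is justified in the Discussion, under Strengths. The sponsor has "powered the study to detect a between groups Cohen’s d effect size of 0.50 on an outcome measure", and defines that effect as the difference between groups in mean change from pre- to post-assessment. The example there has gains of 5.8 and 1.0 index points and a spread of 10 points, described as two thirds of a standard deviation. The total is 120. On sites it adds: "We intend to enroll equally from each site (60 per site").

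The article nowhere names a participant random effect, a repeated-measures structure or a within-person covariance.

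**The concern.** Group by time is a comparison of within-person changes. Its correct error is the variability of change, which is smaller than the variability of two unrelated scores when the same person's results are positively correlated. A mixed model achieves this only if it knows which records belong to the same person. With site as the one random factor, a participant's V1 and V2 scores are independent given site, and all stable variation between people goes into the residual.

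The test that decides efficacy would then be too conservative, and a real effect of the size planned for could be reported as null. The stated maximum likelihood handling of missing data would also lose most of its value: with no link between visits, the V1 score of a person who drops out carries no information about that person's missing V2 score.

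**Working it through.** **Inputs**
- 60 per arm, 1:1 allocation (Overall design and timeline; Randomization).
- Effect d = 0.50 on the change score; example difference 5.8 − 1.0 = 4.8 points (Strengths).
- SD of change 10, equal to 2/3 of an SD, so single-visit SD = 10/(2/3) = 15 (Strengths). The article calls the 10 points a variance. Read as a variance, 4.8/sqrt(10) = 1.52; read as an SD, 4.8/10 = 0.48, close to the stated 0.50. The SD reading is used.
- Two-sided alpha of 0.05 (sidedness assumed); equal SD at both visits and in both arms (assumed).

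**The plan's own figure.** Target power is not stated, so 120 cannot be reproduced exactly. For 80% power at d = 0.50, n per arm = 2 × (1.960 + 0.842)² / 0.50² = 63. With 60 per arm, power = P(Z > 1.960 − 0.50 × sqrt(30)) = P(Z > −0.779) = 78% (77.5% by the t distribution). So 120 is close to an 80% two-sided design on the change score.

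**Standard error of the interaction** (n per arm, single-visit SD = s, pre-post correlation = rho)
- Within-person: SD of change = s × sqrt(2(1 − rho)), so SE = s × sqrt(4(1 − rho)/n).
- Site as the only random term: four independent means, so SE = s × sqrt(4/n). A site intercept common to both visits largely cancels from this contrast.
- Ratio = 1/sqrt(1 − rho).

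**With the article's illustrative figures**
- rho = 1 − 10²/(2 × 15²) = 1 − 100/450 = 0.78.
- Within-person SE = 10 × sqrt(2/60) = 1.83.
- Site-only SE = 15 × sqrt(4/60) = 3.87.
- Ratio = 2.12.
- Site-only power at 5.0 points = P(Z > 1.960 × 2.12 − 2.739) = P(Z > 1.42) = 8%. At 4.8 points it is 6%, against 75% within-person.
- True type I error = 2 × P(Z > 4.16) = 0.00003.
- The site-only model would need about 200 per arm for 80% power at 5.0 points.

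**Sensitivity to the correlation** (d = 0.50 in units of the change SD, 60 per arm, normal approximation)

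| rho | SE ratio | True type I error | Power |
|---|---|---|---|
| 0.5 | 1.41 | 0.0056 | 49% |
| 0.6 | 1.58 | 0.0019 | 36% |
| 0.7 | 1.83 | 0.0003 | 20% |
| 0.78 | 2.12 | 0.00003 | 8% |
| 0.9 | 3.16 | below 0.000001 | below 0.1% |

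At rho = 0.5, a critical value of 1.97 in place of 1.96 gives 48%.

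**Simulation check.** Two sites of 60, SD 15, rho 0.78 and an assumed site SD of 3, fitted both ways, 300 runs per setting. Mean SEs were 3.85 to 3.86 (site only) and 1.81 (participant intercept). At a 5-point effect the rejection rates were 11% and 81%; with no effect they were 0% and 7%. A separate run of 3,000 gave 8.9% (site only) and 78.5% (within-person) with the effect present. These agree with the formulas within simulation error of a few percentage points.

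**The case against.** The strongest reply is that this is one sentence in a condensed article. It does not say that site is the only random factor or that visits are independent. A residual covariance by participant is specified separately from the random factors, so naming site does not exclude one, and the full analysis plan is not shown. The rest of the article points towards a within-person analysis: the design is longitudinal, the same battery is repeated, time is a model factor, and the effect size is defined on change. On this view the sentence is incomplete rather than wrong.

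Much of this stands. A reader might infer that the sponsor chose to ignore the pairing, or that the trial will really run at 8% power. The documents support neither. They do not address the point, and 8% needs both a literal fit and a correlation taken from an example on an index-type score. The primary outcome is an average of six z-scores, for which the article gives no correlation. Covariates admitted at baseline p < 0.1 might also absorb some between-person variance, although they are conditional and do not replace a participant term.

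A reader might also treat the random site effect with two levels as a serious fault. Its variance rests on one degree of freedom and will be poorly estimated, but it hardly touches the interaction.

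What does not stand is that this is only routine condensation. The article lists fixed and random terms for its deciding test, and the list as given does not fit data with two records per person.

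**Conclusion.** The concern holds for the model as stated. Followed literally, the primary test uses a standard error that is too large for any positive pre-post correlation, and it discards the within-person correlation on which the sample of 120 depends. The inflation is about 1.4 times at an assumed correlation of 0.5 and about 2.1 times at the 0.78 derived from the illustrative example. That derivation requires the 10 points to be an SD and the single-visit SD to be 15. Power at d = 0.50 would be about 48% to 49% or about 8% respectively, against about 78% for the analysis the sizing presumes.

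The direction is conservative, so a positive result would not be undermined; the risk is a missed effect. Whether the risk is real depends on the full analysis plan. If that plan already has a participant term, only the published sentence needs correcting.

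**What to change.** State the within-participant structure in the primary model: group, visit and group by visit as fixed effects, with either a participant random intercept or an unstructured covariance across visits within participant. The primary test then matches the change-score basis of the sample size, and the maximum likelihood analysis can use each person's observed scores. If the full analysis plan already says this, align the protocol wording with it.

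Entering site as a fixed effect with two levels is an optional tidy-up with little effect on the interaction test.

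The cost is one sentence and no new data. It should be settled before the data are analysed, because adding the term after a null result would look post hoc.

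### The primary test is a change-score contrast with baseline adjustment left to a p<0.1 imbalance screen; a prespecified baseline-adjusted model would be moderately more precise at almost no cost

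*Protocol article*

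**What the plan says.** The Data analysis section of the protocol article fixes the method in advance. Each outcome is examined with a "linear mixed model with group and time as fixed factors, site as a random factor, and co-variates as necessary from the baseline analysis". The decision rests on one term: "The key value for significance will be the group by time interaction factor for the model".

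Covariates are chosen by comparing the arms on baseline demographic, characterization and outcome variables and on the total time spent using the program. Any that differ at p<0.1 "will be noted and used as covariates in the linear mixed model analysis".

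The visits are also fixed. For the primary question, "we will conduct the analysis based on the pre-training (baseline) and post-training data". For persistence, "we will conduct the analysis based on the pre-assessment (baseline) and follow-up assessment data". A third comparison uses V2 and V3: "We will conduct confirmatory analyses based on the post-assessment (completion) and follow-up assessment data". On incomplete data: "Missing data will be handled with an iterative maximum likelihood procedure to optimally estimate model parameters".

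The Randomization section says that the server "implements the random permuted blocks within strata procedure", with age (65–74, or 75 and over) as the stratum and 1:1 allocation. Age stratum is not among the model terms named. The Strengths section bases the sample size on a between-group difference in post-minus-pre change of d = 0.50, with 120 participants.

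**The concern.** When baseline and V2 are both responses and each arm has its own baseline mean, the interaction subtracts the whole baseline difference from the V2 difference. Unless the regression slope of V2 on baseline is 1, that is more subtraction than is efficient. Conditioning on baseline subtracts only the part that baseline predicts, and under randomisation it estimates the same average treatment difference.

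The p<0.1 rule does not supply this adjustment. It makes adjustment depend on an observed imbalance. When it is triggered, a time-constant main effect does not alter the interaction in complete data. It is also unlikely to bring in age stratum, because stratified allocation balances age by design. And it screens program use time, which is measured after randomisation.

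At stake is a moderate amount of power in a trial whose power is near 80% at best under its own effect size, and whose Weaknesses section expects attrition. A smaller matter concerns V3: participants seen at V2 and lost before V3 contribute no V2 information to the baseline-to-V3 contrast.

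**Working it through.** **Inputs.** From Strengths: d = 0.50 on change; example gains of 5.8 and 1.0 points; a figure of 10 points described as 2/3 of a standard deviation; N = 120. From Overall design: 60 per arm. From Data analysis: significance at 0.05. Assumed: two-sided test; a participant-level term in the model (only site is named as random); equal variances at both visits. The article calls the 10 points a variance. It is read here as the SD of change, because only then does the example come near 0.50: (5.8 − 1.0)/10 = 0.48, whereas 4.8/√10 = 1.52.

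**1. The interaction is a change-score contrast.** Group by time = (mean V2 − mean V1, TAPAT) − (mean V2 − mean V1, control). In one simulated complete dataset, the mixed model with a participant effect gave 7.374 (SE 1.956), and so did the difference in mean change. Adding age as a main effect left both figures the same.

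**2. The plan's own sample size.** No power is stated, so 120 can be neither confirmed nor refuted. With 60 per arm and d = 0.50, the noncentrality is 0.50 × √(60/2) = 2.74. Power is 77.5% by noncentral t (78.2% by normal approximation). By the normal approximation, 80% power needs 63 per arm, or 126.

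**3. Implied correlation.** Ten points is 2/3 of an SD, so SD = 15. Var(change) = 2 × SD² × (1 − ρ), so 100 = 450 × (1 − ρ) and ρ = 0.778.

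**4. Gain from baseline adjustment.** Variance ratio, adjusted to change score = (1 + ρ)/2 = 0.889, a reduction of 11.1%. Residual SD = 10 × √0.889 = 9.43. The same 5-point difference becomes 5/9.43 = 0.530 residual SDs, with noncentrality 0.530 × √30 = 2.90 and power 82.1% (82.8% normal). This is worth 120/0.889 = 135 participants. N for 80% power falls from 126 to 112 (normal). At the example's d of 0.48, power goes from 74.1% to 79.0%.

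**5. Sensitivity to ρ** (d = 0.50 on change, 60 per arm, no loss; unadjusted power 77.5%):

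| ρ | variance ratio | adjusted power (noncentral t) |
|---|---|---|
| 0.5 | 0.75 | 88.0% |
| 0.6 | 0.80 | 85.9% |
| 0.7 | 0.85 | 83.8% |
| 0.778 | 0.889 | 82.1% |
| 0.8 | 0.90 | 81.7% |
| 0.9 | 0.95 | 79.6% |

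**6. With loss.** No dropout rate is given. At an assumed 10% loss (54 per arm), power is 73.8% unadjusted and 78.7% adjusted. At 20% (48 per arm) it is 68.8% and 73.8% (normal approximation, ρ = 0.778).

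**7. V2 data in the baseline-to-V3 contrast.** Three sets of assumed correlations (V1–V2, V1–V3, V2–V3) were used: all 0.78; 0.78, 0.70, 0.78; and 0.78, 0.70, 0.85. With V3 complete, adding V2 changes nothing (ratio 1.000). With 10% missing at V3 the variance ratio is 0.983, 0.976 or 0.960. With 20% missing it is 0.965, 0.952 or 0.919.

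**8. Age stratum.** In 400 simulated trials the older stratum was assumed to score 6 points lower throughout and to gain 2 points less. Mean SEs were 1.835 (change), 1.826 (change with age as predictor of change), 1.754 (baseline-adjusted) and 1.729 (baseline-adjusted plus age).

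**The case against.** The strongest reply is that nothing here is an error. Group by time over baseline and V2 is a valid test under randomisation, and it matches the change-score scale on which the trial was powered. The article is condensed, and an analysis plan not shown may add a participant effect, the age stratum or a covariance structure. All of this stands. The point is therefore not one of missing detail. It rests on what the article itself fixes: the decisive term, the visits and the covariate rule.

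The size is also open to challenge. The correlation of 0.78 comes from an illustrative index-score example, while the actual outcome is an average of six z-scores. The advantage also needs the slope on baseline to be below 1, which equal variances and ρ < 1 ensure. That is why a range is shown; at ρ = 0.9 the gain is only about 2 points of power.

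A reader might infer more than the article supports:

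- **That the analysis is wholly unadjusted.** It is not: the p<0.1 rule can admit covariates, including baseline outcomes. The trouble is that it does so conditionally, and in a form that does not help the interaction.
- **That omitting the age stratum does real damage to the planned test.** An age main effect changes neither the estimate nor its SE. Age as a predictor of change cut the SE by about 0.5% (1.835 to 1.826), under assumed effects.
- **That leaving V2 out always wastes precision at V3.** With complete V3 data it costs nothing. V3 is the secondary time point, and V2 is used in the separate V2-to-V3 analysis.

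**Conclusion.** The point holds as one of efficiency and prespecification, not validity. The fixed primary test gives up about 11% of variance, or 4 to 5 points of power at d = 0.50, relative to a baseline-adjusted analysis of the same data. This assumes a two-sided 0.05 test, a participant-level term, equal variances at both visits, and the SD readings of 10 and 15. Over correlations of 0.9 to 0.5 the gain runs from about 2 to about 10 points.

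The benefits from age stratum (small) and from V2 data in the V3 contrast (about 2% to 8% of variance at an assumed 10–20% loss) are secondary. For V3 the more credible missing-at-random assumption matters as well, since the model can then condition on response at V2.

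It would go too far to conclude that the sample size is wrong. The article states no power, and whether 120 participants suffice depends on a target it does not give.

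**What to change.** For the primary analysis, replace the p<0.1 covariate screen with a prespecified model:

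- The baseline mean is constrained to be common to both arms, with the arm difference at V2 as the primary contrast. Using baseline as a covariate is an acceptable alternative, but the two are not equivalent when data are missing, so the text should name one.
- Age stratum by visit enters as a design factor. The expected gain is small; the reason is to respect the randomisation.
- Preferably, V1, V2 and V3 are fitted as responses in one model with unstructured within-participant covariance. The V3 contrast and the V2-to-V3 change then come from the same fit, and participants lost after V2 still contribute their V2 data.

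The cost is a changed wording of the published primary analysis, a few more parameters at N = 120, and some code. No new data are needed. The change should be made and dated before unblinding.
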